#### Brain MRI

A 3T MRI scanner with a 32 channel receive-only phased-array head coil will be used. As in preliminary work [31, 47], high resolution magnetisation prepared rapid acquisition gradient echo (MP2RAGE) T1-weighted structural data will be acquired to assess grey matter volumes. Resting state functional connectivity in pain networks will be assessed using an EPI sequence and those data will be pre-processed, denoised and analysed using standardized pipelines. Fieldmaps will also be attained in the scanning pipeline to allow for resting state MRI distortion correction. Diffusion weighted images will be obtained using a EPI-sequences with 60 isotropic oriented gradient orientations and various b-values. These data will be processed to assess regional white matter alterations in pain related brain areas. Furthermore, tractography will be performed to analyse structural connectivity within pain networks and to correlate the structural connectivity to functional connectivity obtained by resting state fMRI.

Contention remains regarding the most important functional networks and brain regions that contribute to non-specific LBP. Therefore, we will assess a wide range of variables (Table 1) and prior to deciding which variables that go to further data processing, dimensionality reduction will performed (see Analytical Methods point “A”).

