**Fig 1 pone.0282346.g001:**
[figure not shown]
Approach to artificial intelligence tool implementation. GOÄ: Gebührenordnung für Ärzte (German medical cost database).

Dimensionality reduction will be performed to identify the most relevant variables (of those listed; Table 1) for subgrouping and classification. Given known challenges with data-analytic variable weighting and multidimensional data (e.g. scaling each variable to 0–1) [31], our first step in dimensionality reduction will focus on traditional statistical methods including paired t-tests, analysis of covariance and multicollinearity assessment through correlation analysis [31]. Following this, pending the number of important variables (e.g. if more than 8 variables remain) we will consider variable weighting using a decision tree classifier and targeted projection pursuit with artificial neural networks [91]. The outputs will be used to select the most relevant variables distinguishing non-specific LBP from controls (2-class model).Following determination of the most important variables, pain-free controls will be removed from the data for the following clustering steps. Cluster validation methods [92], including Calinski-Harabasz, Davies-Bouldin and Sillouette values, will be used to determine the optimal number of clusters and variables for the remaining non-specific LBP data. Given the potential for high dimensionality introducing noise and influencing clustering, we will evaluate the outputs of clustering using all outcomes and within individual domains (e.g. in preliminary work [31, 47], psychological and brain MRI variables correlated more highly with each other within their domains than between variable domains). The output of this step will allow us to determine the optimal number of clusters and variables.Based on the information in step B, we will apply fuzzy c-means clustering model [31] of non-specific LBP on either the primary clustering or domain specific clustering. The clusters derived in this step will be used to label classes of non-specific LBP.Outputs from steps B and C in terms of class labels will be used to evaluate non-specific LBP classification. We will apply Support Vector Machine, Naïve Bayes, k-Nearest Neighbour and Random Forest binary/multiclass classifiers as appropriate for the data. Given we are focusing on internal (i.e. on the current dataset, rather than a second newly collected dataset from a different research centre or project) validation of a classification model, validation of the model will be done via k-fold cross validation, as random data-splitting is not generally recommended for internal model validation [93–96]. The output of this will be a sub-grouping tool for people with non-specific LBP assuming availability of all data and tests and no consideration of test cost.We will consider the following sensitivity analyses:

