
we will evaluate random data-splitting and repeat steps B and C to determine if the clustering outputs hold across random samples;we will apply steps B to E within each domain (e.g. brain MRI, psychosocial variables, spine MRI) as required;repetition of analysis only with participants without any imputed data; to examine the potential impact of missing data.consideration of impact of secondary variables (see bottom panel of Table 1) on sub-grouping.the methods of step (D) will be reapplied under constrained cost assumptions, considering financial-cost, time, and patient burden of obtaining each clinical outcome. Financial costs will be according to current rates according to the Gebührenordnung für Ärzte; time will be according to clinical measure and patient burden will be according to an ordinal scale. The output will be a model for most effective sub-group identification for people with non-specific LBP respecting cost/time/burden constraints.consider the findings of sub-grouping when patients with or without radiological evidence of degenerative changes (see Quantitative variables and data collection > Spine MRI) are included.

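### The random-split check repeats steps B and C but not step A, so the sampling stability of the LBP-versus-control variable selection is not tested

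*Protocol article*

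**What the plan says.** The Brain MRI section identifies dimensionality reduction as point A of the analysis: "dimensionality reduction will performed (see Analytical Methods point" A. Under Analytical and statistical methods, that step uses paired t-tests, analysis of covariance and correlation analysis. If too many variables remain, a decision-tree classifier and projection pursuit are considered. Its purpose is stated: "The outputs will be used to select the most relevant variables distinguishing non-specific LBP from controls (2-class model").

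The next step begins: "Following determination of the most important variables, pain-free controls will be removed from the data for the following clustering steps". Step B then applies cluster-validity indices to the LBP data. Of the variable sets to be compared it says: "we will evaluate the outputs of clustering using all outcomes and within individual domains". Of its result it says: "The output of this step will allow us to determine the optimal number of clusters and variables". Step C applies fuzzy c-means clustering, and step D trains classifiers on the resulting labels.

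The sensitivity analysis on random samples is: "we will evaluate random data-splitting and repeat steps B and C to determine if the clustering outputs hold across random samples". Of the other sensitivity analyses, the within-domain one runs from step B onward and the cost-constrained one reapplies step D.

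**The concern.** The variables retained in step A decide what the sub-groups can be made of, which tests the tool needs, and what the cost-constrained model starts from. Step A is also the step most exposed to sampling variation. It reduces a long list of candidates to at most about 8, and the protocol itself says that no single factor separates people with and without LBP, that it is disputed which brain networks matter, and that measures within a domain often correlate. In that setting, variables with nearly equal evidence can change places from one sample to the next.

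A stability check that starts at step B gives every split the same list. That list was chosen using the very participants who make up the split. The check can show whether clusters recur given the list. It cannot show whether another sample would have produced a similar list, or similar clusters once the list is allowed to change.

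**Working it through.** **1. What each stated check can reach**

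| Check | What is rerun | Tests the step A selection across random samples? |
|---|---|---|
| Random data-splitting | B and C | No: the controls are already removed |
| k-fold cross-validation ("validation of the model will be done via k-fold cross validation") | Step D classifier | Not stated that step A sits inside the folds |
| Within-domain analyses | B to E | No |
| Cost-constrained analysis | D | No |
| Complete cases ("repetition of analysis only with participants without any imputed data") | No starting step named; may include A | No: one non-random subset, for missing data |

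**2. The plan's own figure.** The Study size section takes 2^k as the minimum with k up to 8: 2^8 = 256, which reproduces. The target is 300 LBP (300/256 = 1.17) and 300/3 = 100 controls. These figures are not in dispute.

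**3. Number of candidates (a count from Table 1).**
- Spine MRI 16: three disc measures, vertebral fat, four muscle volumes, four muscle fat fractions, four gradings.
- Resting-state connectivity 10: four networks within, six pairs between.
- Grey matter regions 12.
- Two-point discrimination 1, pressure pain thresholds 2, temporal summation 1, laser evoked potentials 4.
- Cognitive-emotional questionnaires 7, Central Sensitisation Inventory 1.

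Sum: 16 + 10 + 12 + 1 + 2 + 1 + 4 + 7 + 1 = 54. Five diffusion measures make it 59. Table 1 leaves the number of connectivity and tract measures open, so this count is approximate.

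**4. Precision of one step A comparison.** Two-sided 0.05, standardised difference d assumed, power approximately Φ(d·√(n1·n2/(n1+n2)) − 1.96). Full sample: √(300·100/400) = 8.66. Random half: √(150·50/200) = 6.12.

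| d (assumed) | 300 + 100 | 150 + 50 |
|---|---|---|
| 0.2 | 41% | 23% |
| 0.3 | 74% | 45% |
| 0.4 | 93% | 69% |
| 0.5 | 99% | 87% |

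For differences of 0.2 to 0.3 SD, whether a variable passes is far from certain even in the full sample.

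**5. Overlap of selected lists (simulation, all effects assumed).** Candidates are ranked by |t| and the top 8 kept. With 59 candidates, chance overlap is 8·8/59 = 1.1.

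| Assumed truth | Shared by two halves, of 8 |
|---|---|
| 59 candidates; differences spread over 0–0.5 or 0–0.8 SD, or 20 variables at 0.5 SD | 2.4–3.3 |
| 59 candidates; exactly 8 differ by 0.5 SD | 5.4 |
| 40 or 59 candidates; 8 differ by 0.3–0.5 SD, or 20 differ by 0.2–0.5 or 0.3–0.8 SD | 3.4–4.7 |
| 40 or 59 candidates; exactly 8 differ by 0.5–0.8 SD | 6.7–7.0 |

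In the last two rows, the two halves gave identical lists in 0% to 29% of runs. Within-domain correlation of 0, 0.3 or 0.4 changed little.

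Full sample against a bootstrap resample: 4.9 to 6.6 of 8 for the settings in the first two rows, and 7.3 to 7.4 where 8 of 59 variables differ by 0.5–0.8 SD. A check that starts at step B shows none of this variation, whichever row is nearest the truth.

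**The case against.** The strongest reply is that the check is coherent for its stated purpose. It asks whether the clustering outputs recur, and holding the inputs fixed is a legitimate way to ask that. Nothing in the article says that the variable list itself will be reported as stable. This stands, and it is why stating the condition openly would be an acceptable alternative to rerunning step A.

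A reader might infer that instability of the chosen variables would never be seen anywhere in the plan. The document does not support that. Step B, which is repeated, also settles the optimal number of variables and compares all outcomes with single domains, so some variation in the variables kept could surface across splits. It is unclear whether all outcomes means the whole of Table 1 or only what survived step A. The complete-case repetition may also rerun step A. But step B works with cluster-validity indices in LBP participants alone, and the complete-case run is not a random-sample check. Neither tests the LBP-versus-control selection.

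The simulations are also fairly criticised:
- A top-8 ranking by |t| is simpler than the planned sequence, and 8 is an upper figure in the plan, not a forced count.
- Two halves exaggerate the instability of a list chosen on the whole sample, and no split size is stated.
- Shared variable names are not the same as shared sub-groups. Swapping one correlated measure for another may move few people between clusters, and no effect on membership has been shown.

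These limits stand. The figures illustrate and do not predict.

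Finally, resampling detail is often left to an analysis plan. Here, though, the article does not stay silent: it names the steps to be repeated, and step A is not among them.

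**Conclusion.** The point holds in limited form. As written, the random-split analysis carries a variable list selected on the full sample into every split, and no other stated analysis tests that selection across random samples. A conclusion that the clusters hold would be conditional on the step A list.

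How much this matters depends on effect sizes that the document does not give. Under the assumptions above, two halves share roughly 2.4 to 7.0 of 8 variables, and the full sample and a bootstrap resample share roughly 4.9 to 7.4. If a handful of variables differ strongly, the list is fairly stable. If many differ modestly, it is not.

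It would go too far to say that the tool rests on an arbitrary list, or that the clusters will prove unstable. The document gives no basis for either. The article limits itself to internal validation and says that further studies are needed. The change should be made, but it corrects a sensitivity analysis and leaves the primary pipeline as it is.

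**What to change.** In the random-splitting sensitivity analysis, name steps A to C in place of steps B and C. In each split or resample:
- Keep each control together with the matched LBP participants (1:3 by the Participants section) so that step A, including its paired tests, can be run. Remove controls only afterwards, as in the main analysis.
- Run step A as a fixed algorithm. Its discretionary parts, such as when to move on to the decision tree and projection pursuit, need stated rules first.
- Report how often each variable is selected, and how well cluster membership agrees with that from the full sample.

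State the split or resample size. A random half has 150 LBP participants, below the protocol's own minimum of 256 for 8 variables, so halves are a harsh test.

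No retention threshold on selection frequency is needed. Such a rule would change the primary selection and is a separate decision.

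If step A is not to be repeated, add one sentence saying that the stability result is conditional on the variables selected in step A on the full sample.

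Cost: computing time, some work to make step A reproducible, and a reported stability that will probably look less favourable. No new data are needed.

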### Confidentiality and data management

Data protection regulations for scientific investigations of the state of North Rhine-Westphalia (§28 DSG-NRW) and the General Data Protection Regulation (Art. 89 DSGVO) will be observed. During measurements with participants in the study, image (DICOM format) and tabulated numerical and string data will be generated (“study data”) in electronic form. Personal data (name, date of birth) will be recorded on a written informed consent form. Each participant will be assigned a random code (e.g. PREDICT34621). This code connects the consent form and the study data. We expect to that up a maximum of 30 GB of data will be generated in the study. Personal data on the consent form will not be saved with the data collected during the study. The consent form containing the personal data and the participant code will be stored separately from the study data at the Hochschule für Gesundheit and will be destroyed by the project management after the study has been completed. The study data is thus pseudonymised until the consent form is destroyed. After destroying the consent form, the study data are anonymized. Participation in the study is voluntary and participants can withdraw at any time and request their data be deleted. After anonymization, however, it is no longer possible to revoke participation since the data can then no longer be assigned to a single person. All study data will be stored electronically in a pseudonymised (later anonymous) form, protected by a password, on the servers of the Hochschule für Gesundheit, Universitätsklinikum Bergmannsheil and/or the Hochschulnetz NRW (“sciebo”). Data obtained at Bergmannsheil Bochum will be stored on site on local servers. In the interest of good scientific practice, the study data will be permanently stored in an anonymous form in online register databases after the study has been completed. Anonymized participant-level tabulated data will be made available permanently on a GDPR-conform data repository, such as www.osf.io and/or as supplemental data with published manuscripts. As a rule, anonymized participant-level tabulated data will be transferred to online register databases when the results are published in specialist journals, but at the earliest after data collection for the study has been completed. This will enable free re-use of the collected data. For MR (DICOM format) image data, access to the image data and re-use will be permitted upon written agreement with the Hochschule für Gesundheit.

### Dissemination policy

Findings from the outcomes of this trial will be reported in journal articles and potentially PhD theses, which will include results regardless of the direction or magnitude of the effect. The results will also be presented at leading national and international conferences, clinical forums and to other relevant health professionals and stakeholders, as well as to the participants. All participants will be able to elect to receive a brief report of their study results via email at the completion of the study. Participants may also receive a copy of their MRI data. If the participant expresses interest in the study results, they can request to have a copy of published articles sent to them.

Consistent with our current practice, the ICJME authorship guidelines [97] will be followed in defining author and non-authors and author roles will be follow the CRediT taxonomy [98, 99]. We will publish the full protocol in a peer-reviewed journal. Anonymized participant-level data and statistical code will be made available on a data repository, such as www.osf.io and/or as supplemental data with published manuscripts.

## Discussion

Based on our recent systematic review [23], our project will be the first larger scale study to assess multiple dimensions of pain contributors with a view to detecting clinically relevant sub-groups in non-specific LBP. We anticipate the production of a comprehensive, multidimensional dataset including imaging of the lumbar spine and the brain, assessment of pain processing, and emotional and psychosocial determinants of pain. This dataset will position us to test the hypothesis that patients with non-specific LBP can be grouped in clusters with common features.

Currently non-specific LBP is viewed as one large all-encompassing diagnostic entity. In our view, the results of the project, if sub-groups do indeed exist, will result in a substantial departure from the current paradigm by taking a fresh, rational perspective to optimise the screening of NSCLBP, which will guide more focused and tailored management. Importantly, should no relevant sub-groups be detected, this will also be a boon for current efforts, in that this will reinforce the need to implement current (generic) approaches, such as reducing medical imaging, for the management of non-specific LBP.

